## Assignment of interventions: Blinding

### Who will be blinded {17a}

Participants are blinded to the main study hypotheses. They are informed that they will be randomized to view one of three different web-based health promotion programs and that each program covers topics related to young men’s physical and mental health and well-being as well as how to deal with stressful situations. In addition, the biostatistician and outcome assessors, who code the B-SAVE data, are blinded to intervention and beverage condition.

### Procedure for unblinding if needed {17b}

We are implementing three interventions during this trial, all of which are educational in nature and designed to affect behavior. There are no circumstances under which unblinding is permissible.

## Data collection and management

### Plans for assessment and collection of outcomes {18a}

Primary, secondary, and tertiary outcome data (see “Outcomes”) are measured using reliable and valid instruments and collected via Qualtrics survey platform at baseline as well as at 6- and 12-months following the completion of the web-based intervention. To promote data quality, several “attention” questions (e.g., “fill in ‘strongly agree” for this question”) are embedded within the Qualtrics survey and are checked by study staff. In addition, even though participants are told that they are allowed to “skip” individual questions, they are also told that they must complete 75% of questions overall and 1005 of the bystander behavior questions to receive compensation. The primary outcome of bystander behavior is also measured during the laboratory session via the B-SAVE VR environment. The BSAVE is a reliable and valid measure of bystander behavior [72].

### Plans to promote participant retention and complete follow-up {18b}

Contact information for participants, including phone numbers, mailing addresses, secondary email addresses, social media handles, and the phone and email of an alternate contact are collected at the time of enrollment to support follow-up efforts. Participants indicate their preferred mode of contact at that time as well. Retention is also prompted by use of an online system (Calendly), which allows participants to schedule their baseline and lab sessions independently by choosing from a variety of openings at different days and times. A text or email reminder is sent to participants 24 h prior to their baseline and lab sessions, with more frequent reminders sent prior to the 6- and 12- month follow-up surveys. During the lab session and after completing their 6-month follow-up survey, participants are asked to review and update their contact information. The incentive structure is also expected to support participant retention in this study. Participants receive $25 for completing the baseline session, $10 per module of the intervention program completed ($40–60 total) plus a $20 bonus if they complete the program within 1-week, $10 per hour for completing the lab session ($30–80 total), $40 for completing the 6-month follow up survey, and $50 for completing the 12-month follow up survey.

### Data management {19}

Two forms of data are being collected during this trial. Survey data collected via Qualtrics survey platform and B-SAVE audio recordings. Following completion of each survey via Qualtrics, study staff examine data validity (i.e., “attention check” items) and completeness. Survey data are stored on Qualtrics servers, which are protected by high-end firewall systems. Data are encrypted using Transport Layer Security (TLS) encryption (also known as HTTPS) for all transmitted data that are downloaded onto password-protected computers by the study PIs. Final datasets will be password-protected. Data management procedures are performed by the study staff.

The second form of data are the audio recordings of B-SAVE responses. Audio files are recorded on computer that operates the B-SAVE. After each laboratory session, these files are uploaded to a password-protected folder on a secure server. B-SAVE recordings are then transcribed and any identifying information is removed. B-SAVE transcripts are then double coded by a team of highly trained coders to ensure reliability.

### Confidentiality {27}

Confidentiality of participants will be protected by assigning participants a unique study identification number (USIN) that will be connected to study data. No personal information will be connected to study data. There will be restricted access to any personal information; personal information will be stored on password protected computers and secure servers separate from data. Only certified study personnel will have access to personal information. Following completion of the study, all identifying information will be destroyed.

### Plans for collection, laboratory evaluation, and storage of biological specimens for genetic or molecular analysis in this trial/future use {33}

N/A. This trial does not include collection of biological specimens.

## Statistical methods

### Statistical methods for primary and secondary outcomes {20a}

Data collected within the virtual environment will be structured as the proportional count of intervention behaviors relative to the number of opportunities to intervene. We will test all Aim 1 hypotheses using generalized linear models based on either Poisson or negative binomial distributions, depending on if a given model is overdispersed. These are appropriate statistical models to use in this case because we expect this proportional count outcome to be positively skewed based on pilot research. We will analyze *Aim 2* RCT data with an intent-to-treat and per protocol analyses. An intent-to-treat analysis includes all participants who were randomized, regardless of compliance, withdrawal, and anything that happens after randomization. An advantage is that it is an analysis based on original randomization; however, effect estimation may be conservative and misleading with increasing attrition. A per protocol analysis considers only participants who fully complied and completed the study. Per protocol is less conservative and may reflect true treatment differences for those with full compliance. Including an intent-to-treat and per protocol analysis will provide a more complete understanding of treatment effects. Outcomes, including prosocial bystander behaviors, will be modeled using a generalized linear mixed model. This is an appropriate statistical model to use with repeated measures data collected over time [73]. Random effects for subject will be included to account for the multiple measurements taken at baseline and 6- and 12-month follow-up on each subject. Intervention condition will be dummy coded, with variables representing both the *RealConsent1.0* and *RealConsent2.0* conditions, with *Taking Charge* as reference group. Planned contrasts will be conducted between *RealConsent1.0* and *RealConsent2.0* groups.

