**Fig. 2 Fig2:**
[figure not shown]
SPIRIT diagram of trial schedule of enrolment, intervention, and assessments. Note: BSAVE (Bystanders in Sexual Assault Virtual Environments), BBS (Bystander Behavior Scale), BSABI (Barriers to Sexual Assault Bystander Intervention); OEIS (Outcome Expectancies for Intervening Scale); BES (Bystander Efficacy Scale); BAS (Bystander Attitudes Scale); SES-SF (Sexual Experience Survey Short Form); ROLBS (Reactions to Offensive Language & Behavior Scale); SEI (Self-Efficacy to Intervene Scale); DDQ (Daily Drinking Questionnaire); AESASVQ (Alcohol Expectancies Regarding Sex, Aggression, and Sexual Vulnerability Questionnaire); CTS (Revised Conflict Tactics Scale); RES (Rape Empathy Scale); DRS (Differential Reinforcement Scale)

Within each of the five at-risk scenarios depicted in the BSAVE, participants are prompted at two points (with a flashing microphone icon) to verbalize their response in that situation—thus providing ten opportunities to intervene in sexual risk situations. A team of research assistants will use audio recordings of participants’ open-ended responses to the risk scenes, as well as non-verbal behaviors captured by the VR system, to code intervention behaviors in response to each risk scenario. The most central code of interest will reflect the presence or absence of intervention attempts (0 = no, 1 = yes) in response to each of the two SV intervention opportunities within each of five risk scenes. An index measure will be created based on these responses that can range from 0 to 10 and will be used in data analyses.

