
#### Participant timeline {13}

##### Sample size {14}

Sample size requirements were determined via a Monte Carlo simulation study based on Aim 2 analysis strategy, which will require a larger sample than Aim 1 analyses. The primary outcome for Aim 2 will be intervention proportion: the number of times each participant engaged in prosocial bystander behavior divided by the number of sexist or violent situations they encountered during a given assessment period. Sample size is therefore based on the number per treatment group needed to detect clinically meaningful effects on intervention proportion. Calculations were based on 80% power, level of significance of .05, and two-tailed statistical tests. Clinically meaningful treatment efficacy was based on previous research [23, 71] and was defined as having between a small and medium effect size between group intervention proportions (Cohen’s *h* ≥ .30). In this RCT, this effect size translated into a 15% point difference between groups, at a minimum, and could potentially translate to a clinically significant increase in bystander intervention for those who receive *RealConsent2.0*. Assuming control participants intervene in approximately 50% of all sexist or violent *non-alcohol* situations they encounter, those who receive RealConsent1.0 will intervene in 65% of those non-alcohol-related situations; those who receive RealConsent2.0 will also intervene in 65% of non-alcohol-related situations. For *alcohol-related* situations, we expect those in control and in RealConsent1.0 to intervene approximately 30% of the time whereas for RealConsent2.0, we expect 45% of the time they will intervene. Based on these proportion differences, a total of 484 participants are needed ~161 in each intervention group). We expect between 20% attrition based on previous work. To achieve adequate power, we estimated a needed sample size of at least 605 to maintain complete data for 484 participants for the per protocol analysis. Additionally, this sample size allows us to detect small differences (7%) in intervention rates within the VR paradigm as a function of intervention and beverage conditions, as well as their interactions.

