## Assignment of interventions: allocation

### Sequence generation {16a}

A separate allocation sequence was created for each site using an automated *stratified block randomization* program implemented through SAS. Participants are stratified by drinking level, resulting in two strata: heavy episodic drinkers (HED) and non-HED. For each stratum, a separate block randomization sequence was used to ensure that equal numbers of men are assigned across the six groups that represent treatment condition (*RealConsent1.0, RealConsent2.0, or Taking Charge)* by beverage condition (Alcohol or Placebo): *(1) RealConsent2.0*/alcohol, (2) *RealConsent2.0*/placebo, (3) *RealConsent1.0*/alcohol, (4) *RealConsent1.0*/placebo, (5) *Taking Charge*/alcohol, or (6) *Taking Charge*/placebo.

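### Aim 1 restricts a score of yes codes out of a fixed ten to Poisson or negative binomial models, so an underdispersed score would be tested with standard errors that are too wide

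*Protocol article*

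**What the plan says.** Under Outcomes {12}, in the text below Fig. 2, each of five risk scenes has two prompts, "thus providing ten opportunities to intervene in sexual risk situations". Each response is coded 0 or 1 for an intervention attempt. The article then states: "An index measure will be created based on these responses that can range from 0 to 10 and will be used in data analyses". The B-SAVE measure is one of the two primary outcomes.

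Under Statistical methods for primary and secondary outcomes {20a}, the virtual-environment data will be "structured as the proportional count of intervention behaviors relative to the number of opportunities to intervene". All Aim 1 hypotheses are to be tested with "generalized linear models based on either Poisson or negative binomial distributions, depending on if a given model is overdispersed". The reason given is that "we expect this proportional count outcome to be positively skewed based on pilot research". The section names no binomial-type model and gives no rule for a score that is less variable than Poisson.

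**The concern.** A sum of ten yes/no codes cannot exceed ten, and its variance shrinks as the rate moves up from zero. A Poisson model ties the variance to the mean, and a negative binomial model can only add to it. The selection rule looks in one direction only: it acts on overdispersion and leaves underdispersion with Poisson.

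Calling the outcome a proportional count does not help. Every man has the same ten opportunities, so the denominator is a constant offset in a log-link model and leaves the variance assumption unchanged. The skew argument does not help either, because a binomial score with a low rate is also right-skewed.

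At stake is the precision of a primary outcome. Sample size {14} says the trial can detect a 7-point difference in virtual-reality intervention rates by programme, by beverage and for their interactions. Over-wide standard errors would erode that ability.

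**Working it through.** **Inputs from the article.** Ten binary codes per man (Outcomes {12}); Poisson, or negative binomial if overdispersed ({20a}); 484 men with complete data and a 7-point difference (Sample size {14}); six equal groups (Sequence generation {16a}). The test level comes from Sample size {14}: "Calculations were based on 80% power, level of significance of .05, and two-tailed statistical tests". That sentence describes the Aim 2 calculation and is carried over here.

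**The plan's own figures.** 484/(1 − 0.20) = 605, as stated. 484/6 = 80.7, about 81 men per cell. The 7-point claim cannot be reproduced, because no virtual-reality base rate or dispersion is given. Both are therefore assumed below, over a range.

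**Variance.** For ten binary codes with rate p and within-man correlation ρ:

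- mean = 10p
- true variance = 10p(1−p)(1+9ρ)
- Poisson variance = 10p

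The two agree only when (1−p)(1+9ρ) = 1, that is, when ρ = p/[9(1−p)]. Below that ρ the score is underdispersed against Poisson. At ρ = 0 the Poisson standard error is too large by the factor 1/√(1−p).

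| p | break-even ρ | Poisson SE too large at ρ = 0 |
|---|---|---|
| 0.1 | 0.1/8.1 = 0.012 | 1/√0.9 = 1.05, 5% |
| 0.2 | 0.2/7.2 = 0.028 | 1/√0.8 = 1.12, 12% |
| 0.3 | 0.3/6.3 = 0.048 | 1/√0.7 = 1.20, 20% |
| 0.5 | 0.5/4.5 = 0.111 | 1/√0.5 = 1.41, 41% |

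Example at p = 0.5, ρ = 0, 81 per cell, log ratio of two means: Poisson SE = √[2/(81×5)] = 0.070; true SE = √[2×0.5/(81×5)] = 0.050.

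**Power for +7 points, 81 per cell, two-sided 0.05.** Scores were simulated as beta-binomial out of ten. The planned rule was taken as Poisson unless the Pearson dispersion exceeds 1, then negative binomial with a moment-estimated dispersion. The comparator is a quasi-binomial logit model. Entries are planned rule v quasi-binomial, in per cent; repeat runs differ by about a point.

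| Base rate | ρ = 0 | ρ = 0.05 | ρ = 0.1 |
|---|---|---|---|
| 10% | 98 v 99 | 92 v 92 | 85 v 85 |
| 20% | 87 v 92 | 78 v 78 | 68 v 67 |
| 30% | 72 v 84 | 67 v 69 | 59 v 58 |
| 50% | 47 v 80 | 46 v 62 | 48 v 53 |

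At ρ = 0.2 and 0.3 the two agree within about 1 point at every rate, including 50%.

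**Type I error of the planned rule.** At a 50% rate it is 0.003, 0.018 and 0.050 for ρ = 0, 0.05 and 0.1. At 10 to 30% with ρ of 0.05 or more it is 0.045 to 0.053. Where it departs from nominal, it does so on the conservative side.

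**Programme contrast pooled over beverage.** With 161 per programme, p = 0.5 and ρ = 0, power is 86% under the planned rule against 98% with an empirical variance.

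**Skew.** Binomial skewness is (1−2p)/√[10p(1−p)]: 0.8/√0.9 = 0.84 at p = 0.1, 0.4/√2.1 = 0.28 at p = 0.3, and 0 at p = 0.5. A bounded binomial score therefore gives the expected positive skew at low rates, while a 50% rate gives none.

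**The case against.** The strongest reply is that the damaging settings are unlikely. The only information in the article on the score's distribution is that positive skew is expected. This points to rates well below 50%, where the loss is small: about 1 point at a 10% base rate. The 50% and 65% rates in Sample size {14} are Aim 2 assumptions about self-reported non-alcohol situations, not the virtual-reality task. Each man also gives all ten responses, two within each scene, so some positive correlation is to be expected. A correlation of about 0.05 removes most of the loss at a 30% rate, and about 0.2 removes it at 50%. All of this stands, and it limits the size of the point.

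It can also be said that the article gives no overdispersion criterion and does not mention robust errors, which a full analysis plan may add. That too is fair, and the planned rule simulated here is one reading of it. A second reading switched to negative binomial on a 5% test and was compared with an empirical variance. It gave the same picture at low correlation, but at ρ = 0.4 and a 30% rate with 80 per cell it lost power as well (20 v 29%). Agreement at very high correlation therefore depends on implementation. But the article does not leave the model open: it names the family, the selection rule and the reason.

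A reader might go further and take the missing site and drinking-level terms as part of the fault, since the article says "Participants are stratified by drinking level, resulting in two strata" within each site. The documents do not support that. A condensed article commonly leaves the covariate list to the analysis plan, and nothing in {20a} excludes those terms.

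**Conclusion.** The point holds in conditional form. The stated model family and one-directional rule do not fit a score bounded at ten out of ten, and the reason given for them does not favour an unbounded count model. If the score is underdispersed, Poisson is kept, intervals are too wide and power is lost. With no within-man correlation and about 81 per cell, the loss for a 7-point difference runs from about 1 point at a 10% base rate to about 12 points at 30%. The 33-point loss at 50% would need a score without the skew that the article expects.

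Two stronger readings are not supported. A reader might infer that every Aim 1 contrast carries a wrong error bar. In fact the approaches agree closely once ρ passes the break-even value by a modest margin. A reader might also infer a risk of false positives; the check shows conservative tests, not inflated error. The sizes rest on assumed rates and correlations, on a beta-binomial score, and on 484 completers split equally over six cells.

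**What to change.** In Statistical methods {20a}, replace the Poisson or negative binomial wording for Aim 1 with one of two models:

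- successes out of ten with a logit link and an estimated dispersion (quasi-binomial, or binomial with robust standard errors); or
- a mixed logistic model on the ten yes/no codes with a participant effect.

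Either respects the bound at ten and removes the need for a data-driven switch between families. It would also help to state the virtual-reality base rate and dispersion behind the 7-point claim, if the pilot work supplies them.

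The cost is small: same data, same sample size, standard software. Results become odds ratios or rate differences instead of rate ratios, and the programme-by-beverage interaction is then tested on the odds scale unless rate differences are specified. The plan should say in advance which measure is primary.

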### Interim analyses {21b}

We do not plan to conduct interim analyses related to any study aims. It is expected that the trial will be terminated upon reaching a target sample size, which affords sufficient power to test the study aims. It is possible, though highly unlikely, that the trial would be terminated due to concerns about the safety and/or welfare of human subjects. In this case, PIs [name] and [name] will make the final decision to terminate the trial in consultation with the Data Safety Monitoring Board.

### Methods for additional analyses (e.g., subgroup analyses) {20b}

N/A. This trial does not include prespecified subgroup analyses.

### Methods in analysis to handle protocol non-adherence and any statistical methods to handle missing data {20c}

Because we will most likely encounter incomplete data due to dropouts and non-response, multiple imputation of missing data will be used to impute missing values based on other available covariates.

### Plans to give access to the full protocol, participant level-data, and statistical code {31c}

Drs. [name] and [name] at Georgia State University will field all requests for the full protocol, data, and statistical code and will ensure that data are made available, when applicable. Access to these data will be provided through the Inter-University Consortium for Political and Social Research (ICPSR). Users will be required to agree to the conditions of use governing access to the public release data, including restrictions against attempting to identify study participants, destruction of the data after analyses are completed, reporting responsibilities, restrictions on redistribution of the data to third parties, and proper acknowledgment of the data source and funders. Within 1 year after the study is completed, all data will be compiled and organized into a single repository at ICPSR. Data will be made publicly available through ICPSR's website. We estimate that this process will be completed no later than 2026.

## Oversight and monitoring

### Composition of the coordinating center and trial steering committee {5d}

[name] and [name] oversee the standardization of procedures across investigators and staff, encompassing both sites. At each site, a dedicated project coordinator supervises project personnel, including temporary student research assistants and support staff, while also facilitating the organization of team project meetings. [name] serves as the primary director of communication for the multisite research team. He ensures that effective communication among study investigators and staff is achieved through various means, including email correspondence, regular weekly site meetings, and monthly team meetings. Recruitment endeavors are regularly monitored by the respective project coordinators at each site. The trial employs online recruitment methods, which involve the use of social media advertisements, outreach initiatives, and targeted email communications. Prospective participants undergo an initial screening process using an online screener, and those meeting eligibility criteria can proceed to schedule a virtual interview for further eligibility assessment. During these eligibility verification sessions, trained staff including student research assistants assess and confirm eligibility status before obtaining informed consent from participants.

### Composition of the data monitoring committee, its role, and reporting structure {21a}

This trial includes a Data Safety Monitoring Board (DSMB) and Data and Safety Monitoring Plan. The DSMB members were chosen by Drs. [name] and [name]. The three voting members were chosen based upon their knowledge of clinical trial methodology, experience with the topical area (i.e., sexual violence risk reduction strategies), and absence of conflicts of interest. They have been appointed for the life of the project.

DSMB meetings are held every 12 months and began the first year of recruitment. Serious adverse events will be reported to the Chair as soon as they occur. The Chair of the DSMB determines whether an in-person meeting or teleconference is needed. Prior to the meetings, a written report containing any study preliminary findings is sent to DSMB members. Preliminary findings are not made available to individuals outside of the DSMB. Each meeting includes time to review the progress of the study and to answer questions from members of the DSMB. Members of the DSMB disclose any potential conflicts of interest, either pre-existing or those that develop during their tenure, to the Principal Investigator and the NIH Project Officer.

In accordance with NIH policy, a data and safety monitoring plan was developed for the proposed study. Co-PIs [name] and [name] provide oversight of all recruitment and study procedures. They also oversee weekly quality assurance checks during recruitment and assessment time periods to ensure recruitment goals and validity of the data. All records pertaining to the study and all of the original and electronic files containing collected data are securely stored. Drs. [name] and [name] are jointly responsible for dissemination of study findings through presentation and publication formats.

The Institutional Review Board at University of Nebraska Lincoln (UNL) serves as the single IRB or record and approved all Informed Consent documents for the study and provides additional oversight of data and safety issues. The study protocol was approved prior to soliciting or consenting any participants. Moreover, the study is reviewed on an annual basis by the UNL IRB with regard to recruitment and retention, and annual reports will be made by the Co-PIs to the DSMB Chair regarding the progress of the proposed project, including any issues pertinent to recruitment, retention, confidentiality, and safety of human subjects. Any incidents that involve a breach of this plan or serious accident/injury will be reported to the DSMB Chair, the IRB chair at UNL, and the NIAAA Safety and Monitoring Board.

The members of the DSMB perform the following activities:Review the research protocol and plans for data and safety monitoring.Review progress of the trial, including analysis of data quality and timeliness; subject recruitment and retention; subject risk versus benefit; and other factors that may affect outcome.Review serious adverse event reports, provide commentary, and provide oversight to ensure that reports are relayed to individual IRBs and to the Office of Human Research Protections (OHRP), as indicated.Review analyses of outcome data and review reports of related studies to determine whether the current study needs to be changed or terminated.Determine whether the trial should continue as designed, should be changed, or should be terminated based on the data and make recommendations to the NIH and the Institutional Review Board considering conclusion or continuation of the study.Protect the confidentiality of the trial data and the results of the monitoring.Determine whether and to whom outcome results should be released prior to the reporting of study results.Following DSMB meetings, provide appropriate NIH staff with written information concerning their findings.

